# 1.- SUMMARY

## 1.0. TYPE OF APPLICATION

Clinical trial including a marketed investigational product under different conditions from the authorised.

## 1.2. TITLE OF THE CLINICAL TRIAL

PILOT STUDY TO ASSESS THE EFFICACY AND SAFETY OF SWITCHING PROTEASE INHIBITOR TO ETRAVIRINE IN HIV-1-INFECTED SUBJECTS WITH VIREMIA SUPPRESSION

## 1.3. PROTOCOL CODE

ETRA-SWITCH

## 1.6. ETHICS COMMITTEE APPROVING THE TRIAL

CEIC Hospital Universitari Germans Trias i Pujol.

## 1.8. EXPERIMENTAL DRUG

Intelence ® - Etravirine 100mg tablets (400 mg dissolved in water every 24 h)

## 1.10. CLINICAL TRIAL PHASE

Phase III, pilot study.

## 1.11. OBJECTIVE

To compare the virological efficacy of etravirine-based regimen with standard PI-containing regimens.

## 1.12. STUDY DESIGN

A 48 week randomized, active controlled, open-label, parallel, proof-of-concept pilot clinical trial.

## 1.13. STUDY PATHOLOGY

Patients with HIV-1 infection.

## 1.14. PRINCIPAL ASSESSMENT VARIABLE

Viral load.

## 1.15. TYPE OF POPULATION AND NUMBER OF PATIENTS

HIV-infected patients on HAART regimen including a protease inhibitor and at least two nucleos/tide inhibitors.

A total sample size of 40 patients: 20 in Control group and 20 in Etravirine group.

## 1.16. DURATION OF TREATMENT

48 weeks.

## 1.17. CALENDAR AND CONCLUSION DATE

The foreseen date of the inclusion of the first patient is January 2010 and the conclusion of treatment of the last patient will be, approximately, June 2011. The final report will be presented on June 2012.

# 3.- GENERAL INFORMATION

## 3.1. TRIAL IDENTIFICATION

Code: ETRA-SWITCH

Title of the study: PILOT STUDY TO ASSESS THE EFFICACY AND SAFETY OF SWITCHING PROTEASE INHIBITOR TO ETRAVIRINE IN HIV-1-INFECTED SUBJECTS WITH VIREMIA SUPPRESSION

## 3.2. TYPE OF TRIAL

Clinical trial including a marketed investigational product under different conditions from the authorised.

## 3.3. DESCRIPTION OF THE STUDY PRODUCTS

Intelence ® - Etravirine 100mg tablets (400 mg dissolved in water every 24 h)

## 3.5. TECHNICAL DIRECTOR SUPERVISING SAMPLE PREPARATION AND CONTROL

The technical director from the manufacturer lab (Janssen-Cilag SpA).

## 3.8. TECHNICAL SERVICES

Biochemistry, Haematology, Viral Load and CD4 counts will be performed in the central laboratories of the participating Hospital.

Genotypic test will be done in the irsiCaixa Retrovirology Laboratory.

## 3.9. EXPECTED TRIAL DURATION

The maximum study duration will be 72 weeks: 24 weeks of inclusion and 48 weeks of follow-up.

# 4.- RATIONALE AND AIMS

## 4.1. RATIONALE

Etravirine is a second generation non-nucleoside analogue reverse transcriptase inhibitor (NNRTI) approved by the U.S. Food and Drug Administration (FDA) in January 2008 and by the European Medicines Agency in September 2008 for clinical use in adults with incomplete virologic suppression and resistance to previous NNRTI and other antiretroviral classes. 1,2

Etravirine has shown *in vitro* activity against viral strains with mutations that confer resistance to efavirenz and nevirapine.2 However, etravirine's activity is strongly affected by the number of NNRTI mutations present, as well as by the specific mutations. For this reason, in the clinical practice it is important to discontinue the NNRTI as early as possible in patients who have developed resistance to a first-generation NNRTI, in order to prevent the selection of additional resistance mutations that would diminish the efficacy of etravirine.3

The clinical recommendation for market authorization of etravirine was based on the results of two pivotal phase 3 studies, DUET-1 and DUET-2, and four supportive phase 2b trials. Both DUET studies were randomized, double-blind, placebo-controlled, international trials. These studies were designed to evaluate the long-term efficacy, tolerability, and safety of etravirine compared to placebo as part of optimized background regimen including darunavir/ritonavir (DRV/rtv) in treatment-experienced HIV-1 infected subjects with NNRTI resistance after failure of an initial NNRTI-based regimen. The arm including etravirine showed high rates of viral suppression and the likelihood of virologic failure in the etravirine group was correlated with the number of baseline NNRTI and nucleoside analogue reverse transcriptase inhibitor NRTI mutations.4,5,6,7,8

Based on these results, the use of etravirine should not be recommended with 2-NRTIs without additional active agents in patients with NNRTI resistance mutations.3,4

Additionally, etravirine is a substrate and induces of CYP 3A4, as well as being a substrate and inhibitor of 2C9, and 2C19, with a complex drug interaction potential. Pharmacokinetic studies show either etravirine or the co-administered antiretroviral may be significantly affected when used in combination. As a result, etravirine is not recommended to be used with any unboosted protease inhibitor (PI).

A question not yet explored is whether subjects with sustained undetectable HIV-1 RNA-levels experiencing antiretroviral-related toxicity can safely switch their current PI to etravirine. This treatment strategy could allow improvements in tolerability and lipid profile and would permit an easy posology. We designed a proof-of-concept study to test the efficacy and safety of switching from a PI to etravirine in subjects with viral suppression as an antiretroviral strategy of simplification therapy, based on the high antiviral potency, low toxicity, together with its easy posology (even in water dissolution).

***Hypothesis***

- Hypothesis 1. Switching from a PI to etravirine, as a simplification strategy, in subjects with maintained viral suppression will be associated with comparable rates of virological suppression.
- Hypothesis 2. Switching to etravirine in this clinical context will be associated with an improvement of lipid parameters and patient’s satisfaction in comparison with remaining on the previous PI-based regimen.

## 4.2. AIMS

Primary objective:

To compare the virological efficacy of etravirine-based regimen with standard PI-containing regimens.

Secondary objectives:

To compare the immunological efficacy of etravirine-based regimen with standard PI-containing regimens.

To compare the tolerability and toxicity of etravirine-based regimen with standard PI-containing regimens.

To compare the cardiovascular risk of etravirine-based regimen with standard PI-containing regimens.

To compare patient’s satisfaction of etravirine-based regimen with standard PI-containing regimens.

# 5.- TYPE OF CLINICAL TRIAL AND DESIGN

## 5.1. CLINICAL TRIAL DEVELOPMENT PHASE

Phase III, pilot study.

## 5.2. CLINICAL TRIAL DESIGN

A 48 week randomized, active controlled, open-label, parallel, proof-of-concept pilot clinical trial.

## 5.3. RANDOMIZATION AND STRATIFICATION PROCESS

Patients receiving a triple-drug standard HAART PI-based and will be randomly assigned in a 1:1 ratio:

- To switch from the PI to Etravirine (Etravirine group), or
- Continue with the same regimen (Control group).

No stratification process will be used.

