## 6.2. INCLUSION CRITERIA

1. Adult patient having a diagnosis of HIV-1 infection.
2. Antiretroviral therapy started at least 12 months before, always with a HAART combination including 2 NRTIs plus a PI
3. Current HAART combination including 2 NRTIs plus a PI.
4. Maintained undetectable plasma HIV-1 RNA (VL < 50 copies/mL) since the beginning of antiretroviral therapy, for at least 6 months.
5. Absence of suspected or documented resistance mutations in the RT associated to NNRTIs or to any NRTI.
6. Patient having at least one of the following conditions:

- Dyslipemia (LDL cholesterol >130 mg/dL or triglycerides > 350 mg/dL) derived from their current PI regimen or current use of lipid lowering agents due to dyslipemia,
- Antiretroviral-related gastrointestinal disturbances, or
- Low patient’s satisfaction associated with the current regimen posology (BID regimen, ritonavir use, ritonavir intolerance…).

1. Good treatment adherence.
2. Voluntary written informed consent.

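### Unstratified allocation and an unadjusted lipid comparison, with a lipid problem as one of three alternative entry routes, cost avoidable precision on the secondary lipid endpoints (minor recommendation)

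*Protocol*

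**What the plan says.** Section 5.3 has patients "randomly assigned in a 1:1 ratio" and adds "No stratification process will be used". It describes no blocking. Section 1.15 fixes the size: "A total sample size of 40 patients: 20 in Control group and 20 in Etravirine group".

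Inclusion criterion 6 in section 6.2 asks for "Patient having at least one of the following conditions". The first is "Dyslipemia (LDL cholesterol >130 mg/dL or triglycerides > 350 mg/dL) derived from their current PI regimen or current use of lipid lowering agents". The second is gastrointestinal disturbance related to antiretrovirals, and the third is low satisfaction with the current posology. The routes may overlap, and a lipid problem is not required of everyone.

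Hypothesis 2 in section 4.1 expects the switch to be "associated with an improvement of lipid parameters" compared with staying on the PI. Section 8.1.3 lists, all under secondary objectives, lipid changes from baseline to week 48, starts and withdrawals of lipid-lowering drugs, and change in SCORE. The primary objective is virological.

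Section 12.2 compares lipid slopes by Student's t, Wilcoxon or Mann-Whitney tests. It allows a split by some further baseline factor but does not name one. The final analysis is restricted to patients who complete 48 weeks.

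**The concern.** The sample is by design a mix of patients with and without a lipid problem, and that status is known before allocation because it is an eligibility criterion. It bears on three secondary endpoints at once:

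- Patients with LDL above 130 mg/dL or triglycerides above 350 mg/dL have more room to fall. Those selected on a high value also tend to drift towards the mean on retesting.
- Only patients already on a lipid-lowering drug can withdraw one.
- SCORE takes in cholesterol along with other risk factors.

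If one arm happens to receive clearly more of these patients, the lipid, lipid-drug and SCORE comparisons all move together. At 20 per arm the reader then cannot easily separate the effect of the switch from the make-up of the arms. The tests named in section 12.2 do not adjust for this. Because the trial is open-label, a baseline factor chosen after the imbalance has been seen would carry less weight than one named in advance.

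**Working it through.** **Inputs.** 40 patients, 20 per arm (sections 1.15, 6.4 and 12.4); 1:1 allocation without stratification (5.3). The protocol states no imbalance probability, so there is no figure to reproduce.

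**Assumptions, not in the protocol.** K, the number of the 40 who enter by the lipid route, lies between 10 and 30. The arms are exactly 20 and 20. A gap of 4 patients (4/20 = 20 percentage points, for example 12 against 8) is taken as a noticeable imbalance, and 6 patients (30 points) as a large one.

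**Formula.** With x lipid-route patients in one arm, P(x) = C(K, x) · C(40 − K, 20 − x) / C(40, 20). The gap between arms is |2x − K|.

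**Worked case, K = 20.** A gap below 4 means x = 9, 10 or 11, with probabilities 0.2047, 0.2476 and 0.2047, which sum to 0.657. So P(gap ≥ 4) = 1 − 0.657 = 0.343.

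**Across K.** The gap has the same parity as K. For odd K the smallest gap of at least 4 is therefore 5, and the probability is lower. Values are symmetric about K = 20.

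| K | P(gap ≥ 4) | P(gap ≥ 6) |
| --- | --- | --- |
| 10 or 30 | 0.273 | 0.065 |
| 11 or 29 | 0.155 | 0.031 |
| 14 or 26 | 0.320 | 0.096 |
| 15 or 25 | 0.191 | 0.048 |
| 19 or 21 | 0.205 | 0.056 |
| 20 | 0.343 | 0.113 |

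Over every K from 10 to 30, P(gap ≥ 4) runs from 0.155 to 0.343 with mean 0.25, and P(gap ≥ 6) runs from 0.031 to 0.113.

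**Other allocation assumptions.**

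- If K is itself random, with each patient having probability p of the lipid route, P(gap ≥ 4) is 0.164 at p = 0.2 or 0.8, 0.226 at 0.3 or 0.7, and 0.268 at 0.5.
- Under simple randomisation with arm sizes free to vary, a difference of 20 points or more has probability 0.18 at p = 0.3 or 0.7 and 0.22 at p = 0.5.

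**With stratified blocks.** Blocks of 4 within each stratum (an assumed size) leave at most one incomplete block, so the lipid-route gap is at most 2 patients and P(gap ≥ 4) is 0. In general the limit is half the largest block size.

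**What the stratum does not balance.** It pools drug users with untreated dyslipidaemic patients. Suppose there are 10 users (an assumption). If the stratum holds 20 patients split 10/10, the same formula gives P(arms differ by ≥ 4 users) = 0.179. If it holds 30 patients split 15/15, it gives 0.245. Without stratification it is 0.273. Stratifying on the pooled route helps with users only in part.

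**The case against.** Leaving a 40-patient exploratory pilot unstratified is a legitimate choice, and section 5.3 declares it openly. Section 12.4 presents the trial as groundwork for later, properly powered studies. The affected endpoints are secondary. Chance imbalance neither biases a randomised comparison nor inflates its unconditional type I error. Lipid and SCORE endpoints are already changes from baseline, section 12.1 would show any imbalance by arm, and covariate detail may sit in a statistical analysis plan that is not at hand. Because section 12.2 analyses completers, balance at randomisation may not fully survive into the analysed set.

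Most of this stands, and it is why the point is a recommendation and not an error. It does not remove the point. Change from baseline does not equalise room to fall, although some drift towards the mean may already occur between screening and baseline. It also does nothing for the number of patients able to withdraw a drug. The tests that section 12.2 does name are unadjusted.

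A reader might infer two stronger things. One is that the arms have a one-in-three chance of clear imbalance. That is the top of the range, reached only for even K near the middle with arms fixed at 20/20, and the protocol gives neither the entry mix nor a threshold. The other is that only lipid-route patients can show a lipid effect. Lipids are measured in everyone, and patients entering by the other routes can change too. Those who qualify through drug use may have controlled lipids and less room to improve.

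**Conclusion.** The point holds as a minor recommendation. Section 5.3 rules out stratification on a factor known at entry, and section 12.2 names only unadjusted tests for the lipid comparison that Hypothesis 2 rests on. On the assumptions of 10 to 30 lipid-route patients and arms of exactly 20, a gap of 4 or more such patients has about a one-in-four chance (16% to 34%) and a gap of 6 or more a 3% to 11% chance. The 4- and 6-patient thresholds are judgements.

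The loss is precision and interpretability for the lipid, lipid-drug and SCORE endpoints. The documents do not support reading it as bias in the randomised comparison, as a threat to the virological primary endpoint, or as a contradiction within the protocol.

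**What to change.** In section 5.3, replace the sentence on stratification with 1:1 permuted blocks of varying, undisclosed size, stratified by one factor: whether the patient meets the lipid condition of criterion 6 (dyslipidaemia or lipid-lowering drug use), yes or no. Varying and undisclosed sizes matter because the trial is open-label.

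In section 12.2, compare lipid and SCORE changes by a model adjusted for the baseline value, the stratum and lipid-lowering drug use at baseline. Report drug withdrawals among baseline users and new starts among baseline non-users, since the pooled stratum does not itself balance users.

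The cost is two randomisation lists instead of one, and incomplete blocks may leave totals such as 21 and 19. No extra patients or procedures are needed. The stratification must be in place before allocation begins; the adjusted analysis and the split reporting can still be specified later, before the data are examined.

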## 5.4. STUDY DURATION

The total duration of the study will be 72 weeks: 24 weeks for patient inclusion and 48 weeks of follow-up once the last patient is included.

## 5.6. STUDY PLAN

Subjects fulfilling the inclusion criteria will be asked to participate in this study and if they agree, signed informed consent will be obtained. After accepting the participation, patients would be randomized and assessed the first visit. Study visits will be at weeks 4, 12, 24, 36 and 48.

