## 5.7. MASKING TECHNIQUE

Not applicable, since this has an open clinical trial design.

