**Secondary objectives:**

To compare the immunological efficacy of etravirine-based regimen with standard PI-containing regimens.

- Changes in CD4+/CD8+ T lymphocytes at week 48 from baseline.

To compare the tolerability and toxicity of etravirine-based regimen with standard PI-containing regimens.

- Changes in lipid parameters (total, HDL-, LDL-cholesterol and triglyceride levels) at week 48 relative to baseline values.
- Changes in the administration of lipid-lowering drugs throughout the study (new administrations or the withdrawal of previous lipid-lowering drugs).
- Percentage of patients who withdraw from the study.
- Percentage of patients who withdraw from the study due to toxicity.
- Percentage of patients with toxicity ≥ grade 3.

To compare the cardiovascular risk of etravirine-based regimen with standard PI-containing regimens.

- Changes in cardiovascular risk estimated by changes in the SCORE equation at week 48 relative to baseline values.

To compare patient’s satisfaction of etravirine-based regimen with standard PI-containing regimens.

- Changes in patient’s satisfaction at week 48 from baseline, using a 100 mm analogue visual scale.

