## 8.3. TRIAL DEVELOPMENT

After accepting the participation, patients would be assessed the first visit. Study visits would be at entry (BL) and weeks 4, 12, 24, 36 and 48.

Plasma samples will be stored at –80ºC.

Viral load, complete blood count, CD4 cells count, and a complete biochemistry and haematology will be performed at every visit (except for week 4 where only CD4 count and viral load will be performed).

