**Flow chart of study procedures:**

|  | SCR | BL | Wk 4 | Wk 12 | Wk 24 | Wk 36 | Wk 48 |
| --- | --- | --- | --- | --- | --- | --- | --- |
| Informed consent |  |  |  |  |  |  |  |
| Pregnancy test |  |  |  |  |  |  |  |
| Clinical visit |  |  |  |  |  |  |  |
| HIV1-1 Viral load |  a |  |  |  |  |  |  |
| CD4 cell count |  a |  |  |  |  |  |  |
| Biochemistry (including lipid profile) |  a |  |  |  |  |  |  |
| Haematology |  a |  |  |  |  |  |  |
| Patient’s satisfaction |  |  |  |  |  |  |  |
| SCORE equation (blood pressure) |  |  |  |  |  |  |  |
| Adverse events |  |  |  |  |  |  |  |
| Plasma sample storageb |  |  |  |  |  |  |  |

a A blood test including HIV-1 RNA, CD4+ counts, biochemistry and haematology performed within 3 months previous to the baseline visit will be accepted as screening.

b Genotypic resistance testing will be performed to all participants experiencing virologic failure during the study.

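### Section 5.6 places randomisation before the baseline visit in an open-label trial, and nothing requires the satisfaction scale to be completed before the allocation is known, so that endpoint is open to bias

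*Protocol*

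**What the plan says.** Four parts of the protocol bear on the point.

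- **Order of entry (5.6).** Once consent is signed, "After accepting the participation, patients would be randomized and assessed the first visit". This is the only sentence that places randomisation relative to the first visit.
- **Restatement (8.3).** The same step appears without randomisation: "After accepting the participation, patients would be assessed the first visit". The next sentence makes the first visit the baseline: "Study visits would be at entry (BL) and weeks 4, 12, 24, 36 and 48".
- **Masking (5.7).** "Not applicable, since this has an open clinical trial design".
- **Endpoint (8.1.3) and hypothesis (4.1).** The secondary endpoint is "Changes in patient’s satisfaction at week 48 from baseline, using a 100 mm analogue visual scale". Hypothesis 2 expects improvement in lipids and in "patient’s satisfaction in comparison with remaining on the previous PI-based regimen".

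Under 6.2, dissatisfaction with the current regimen's dosing is one of three alternative qualifying conditions. The flow chart's footnote a lets a blood test from before baseline serve as screening, but it does not mention satisfaction. The flow chart has a satisfaction row and separate screening and baseline columns. Its visit marks are not readable in the copy reviewed.

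**The concern.** A change score needs a starting value that treatment assignment has not influenced. Satisfaction on a visual analogue scale is a subjective rating, and some patients enter because they dislike the regimen they are rating. If such a patient has just heard that the protease inhibitor will be replaced, or that it will continue, the mark on the scale may reflect that news as well as past experience.

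Randomisation balances what comes before it. It cannot balance a baseline taken after the allocation is known. Any difference created at that moment enters the endpoint as if it were a treatment effect, with the opposite sign. Statistical adjustment does not fully remove it, because the covariate itself has then been affected by assignment. What is at stake is the satisfaction part of Hypothesis 2.

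**Working it through.** The protocol states no figure to reproduce here. It gives no SD, correlation, significance level or power for satisfaction, and section 12.4 justifies 40 patients only as a pilot. The check has two parts: what the text permits, and how sensitive the endpoint would be.

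**1. Reading the sequence.** Taken together, 5.6, 8.3 and 5.7 give: consent, randomisation, first visit (which is baseline), no masking. Nothing readable places the satisfaction scale before disclosure. The text therefore permits scoring with the allocation known, but it does not say that this happens.

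**2. How a shift enters the endpoint.** Let b be the mean baseline difference (etravirine minus control) caused by knowing the allocation.

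- Unadjusted difference in change = true effect − b.
- Baseline-adjusted difference (ANCOVA, equal variances at both times) ≈ true effect − rho × b, where rho is the correlation between baseline and week 48.

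For b = 10 mm and rho from 0.3 to 0.7, adjustment leaves 3 to 7 mm of bias.

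**3. Inputs.** From the protocol: 20 patients per arm (6.4, 12.4). Assumed: SD 25 mm (range 20 to 30), rho 0.5 (range 0.3 to 0.7), a shift of 5 or 10 mm, and a two-sided 5% test with a normal approximation.

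**4. Standard error of the difference in change.**

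SE = SD × √(2(1 − rho)) × √(2/20) = 25 × √(2 × 0.5) × 0.316 = 7.9 mm.

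**5. Rejection probability when there is no true effect.**

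P = P(Z > 1.96 − |b|/SE) + P(Z < −1.96 − |b|/SE).

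- |b| = 5: 5/7.91 = 0.632, so P = 0.092 + 0.005 = 0.097.
- |b| = 10: 10/7.91 = 1.265, so P = 0.243 + 0.001 = 0.244.

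| Assumed SD, rho | SE (mm) | 5 mm shift | 10 mm shift |
|---|---|---|---|
| 30, 0.3 | 11.22 | 7.3% | 14.5% |
| 25, 0.5 | 7.91 | 9.7% | 24.4% |
| 20, 0.7 | 4.90 | 17.5% | 53.2% |

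The first and last rows are the extremes of the range examined.

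**6. Direction.** The formula depends only on the size of b, but the excess rejections fall on one side. If hopeful switchers score higher and disappointed controls lower, b is positive and the bias works against etravirine. At b = +10 mm nearly all of the 24.4% would then favour the protease inhibitor, and the chance of a false finding for etravirine falls from 2.5% to about 0.06%. If switchers instead mark down the drug they are leaving, b is negative and the excess favours etravirine.

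**7. With the order fixed.** If the scale is completed before disclosure, b = 0 by design, and rejection from this source stays at 5%.

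**The case against.** The strongest reply is that the protocol never says when the scale is completed relative to disclosure. Section 5.6 can be read as one occasion on which both steps occur, with the order inside it left open. Section 8.3 does not place randomisation, and the flow chart, which might settle the matter, cannot be read. A reader might infer that baseline satisfaction is in fact scored with the allocation known and that the endpoint is biased. The documents do not support that. They support only that the written order permits it and that nothing readable rules it out.

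A reader might also take the rejection rates as the risk of a false claim for etravirine. They are not. The most natural mechanism, hopeful switchers and disappointed controls, would work against etravirine, and the protocol gives no basis for either size or direction.

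A third tempting inference concerns viral load: since baseline blood is drawn after allocation, a patient already viraemic could be randomised and later counted as a failure. That risk does not come from the order of steps. It comes from footnote a, under which a blood test "performed within 3 months previous to the baseline visit will be accepted as screening". Such patients would fall into either arm by chance. A same-day reorder that does not wait for the result would not exclude them. Sections 6.2 and 6.3, which require sustained suppression and exclude recent blips, also limit how often this could occur. The viral-load argument is not part of this point.

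It is also fair to say that satisfaction is one secondary endpoint in an exploratory pilot, that Hypothesis 2 also covers lipids, whose laboratory baselines are far less exposed, and that week 48 ratings stay unmasked whatever is done at baseline. All of this limits the importance of the point. None of it justifies leaving an avoidable second source of bias in place.

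**Conclusion.** The point holds as a weakness in the stated sequence. The only sentence that places randomisation puts it ahead of the baseline visit in an unmasked trial, and the satisfaction change score is therefore open to bias of unknown size and direction. The documents do not show that bias will occur.

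The effect is confined to a subjective secondary endpoint. Under the central assumptions, a 10 mm shift takes two-sided rejection under no effect from 5% to about 24%, with about 14% to 53% over the range examined. The SD, correlation and shift are all assumed, so these figures show sensitivity and do not forecast an error rate. Baseline adjustment would reduce the bias to about rho times the shift, half of it at a correlation of 0.5, without removing it.

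The change is worth making because it is nearly free and because no later analysis can recover a baseline recorded before the allocation was known.

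**What to change.** Amend 5.6, and 8.3 to match, along these lines: after consent, all baseline assessments are completed, the satisfaction scale in particular; only then is the patient randomised and the allocation disclosed. If randomisation has to come earlier for practical reasons, it is enough that the allocation is withheld until the scale is complete. The flow chart should show the first satisfaction score at that point.

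The cost is the order of steps on the same day, with no extra visit, test or patient. The change protects the baseline score only. The week 48 rating remains unmasked, and the report should say so when it interprets satisfaction.
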